**Obrigado pela colaboração.**

**Anexo V**  **Versão 04, Outubro 2023**

**Implementação da técnica de tinta da China em urina para triagem laboratorial *point-of-care* da Criptococose em pacientes adultos infectados por HIV no sul de Moçambique.**

**QUESTIONÁRIO**

**Código ___ ___ ___/_______/_____/202___**

**AVALIAÇÃO DA INTERVENÇÃO**

**(Clinico)**

1. **As ferramentas disponibilizadas no treino são mais esclarecedores no âmbito de diagnóstico e tratamento da criptococose**

Concordo fortemente Concordo Neutro Descordo Descordo fortemente

1. **A intervenção é uma alternativa recomendável para triagem laboratorial da Criptococose**

Concordo fortemente Concordo Neutro Descordo Descordo fortemente

1. **Desde a sua implementação o teste da tinta-da-China a partir da urina esteve sempre disponível no Hospital**

Concordo fortemente Concordo Neutro Descordo Descordo fortemente

1. **Qualidade dos serviços melhorou com o novo diagnóstico laboratorial**

Concordo fortemente Concordo Neutro Descordo Descordo fortemente

1. **Pode-se estimar a percentagem de pacientes beneficiados pela intervenção em:**

 100%  80 – 99% 50 – 79%  <50%

1. **Avalie a sua satisfação em relação ao diagnostico laboratorial com a técnica da tinta da China usando a urina**

Muito satisfeito Satisfeito Neutro insatisfeito Muito insatisfeito

1. **Avalie a sua satisfação em relação a disponibilidade do pessoal do laboratório quando você tenta contatá-los?**

Muito satisfeito Satisfeito Neutro insatisfeito Muito insatisfeito

1. **Avalie a sua satisfação em relação ao tempo de resposta do laboratório**

Muito satisfeito Satisfeito Neutro insatisfeito Muito insatisfeito

1. **Avalie a sua satisfação em relação ao formulário de solicitação dos enxames laboratoriais**

Muito satisfeito Satisfeito Neutro insatisfeito Muito insatisfeito

1. **Avalie a sua satisfação em relação a clareza, legibilidade e integridade do resultado do laboratório relatório?**

Muito satisfeito Satisfeito Neutro insatisfeito Muito insatisfeito

1. **A qualidade do diagnóstico foi consistente em todos os turnos? (horário de trabalho, fim de semana, feriado, plantão noturno)**

Concordo fortemente Concordo Neutro Descordo Descordo fortemente

1. **Na sua opinião em qual turno, a qualidade do serviço do laboratório foi comprometida?**

Horário de trabalho Fim de semana Feriado Plantão noturno NA

1. **O número de pacientes internados devido a complicações associadas a meningite criptocócica reduziu com a introdução da nova abordagem do diagnóstico**

Concordo fortemente Concordo Neutro Descordo Descordo fortemente

1. **Com a introdução da nova abordagem do diagnóstico o número de óbitos reduziu**

Concordo fortemente Concordo Neutro Descordo Descordo fortemente

1. **A nova abordagem do diagnóstico contribuiu para que maior número de indivíduos vivendo com HIV tivessem oportunidade de testar para *Criptococcus***

Concordo fortemente Concordo Neutro Descordo Descordo fortemente

1. **O tratamento de pacientes com meningite criptocócica melhorou com implementação da nova abordagem para diagnóstico laboratorial**

Concordo fortemente Concordo Neutro Descordo Descordo fortemente

1. **Avalie na generalidade a sua satisfação em relação a intervenção no seu hospital**

Muito satisfeito Satisfeito Neutro insatisfeito Muito insatisfeito

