**Quantitative data analysis**

Quantitative data will be analyzed using the R studio statistical package. Univariate descriptive analyses will be carried out (mean or median age, standard deviation and variance will be calculated), percentage frequencies of the following variables: tests requested, doctors/laboratory technicians who adhered to the intervention, chi-square to check for associations between the intervention/test and the variables (level of education of the professional, availability of the test, severity of the disease and gender) and logistic regression to estimate the relationship between adherence to the test and factors severity of the disease, work overload in the US/laboratory, level of education of the professional, shift, gender, availability of laboratory services.

A Likert scale will be used to assess the level of satisfaction of all those involved in the intervention (doctors and laboratory technicians) during the study period. And the frequencies of the information obtained will be calculated.

The results will be described and presented in tables and graphs using the Microsoft Excel program. A p-value of <0.05 will be considered significant.

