# To implement the technique of laboratory diagnosis of cryptococcosis using the China ink method in urine as a point of care in selected hospitals in three southern provinces of Mozambique.

This is a stepped wedge trial. Sampling will be non-probabilistic by convenience in relation to the study sites and purposive in relation to the participants.

The study will be carried out in six hospitals (MCH, MGH, JMGH, MPH, XPH, and CHC) over six months. The Adaptation Phase will be the beginning of the iteration with the new test, the healthcare professionals (clinicians in medical service and laboratory technicians assigned to the microbiology sector) adapt to the workflow associated with the intervention (Figure 2). During the three months of adaptation, the researcher will carry out training on the care, diagnosis and treatment of cryptococcosis using urine dye (5 to 20 ml of the sample) with intentionally selected healthcare professionals, the diagnostic guide tools will be provided and an information-sharing workflow will be established between the laboratory and the clinicians.

It's up to the clinician to decide which patients to ask for a urine sample to diagnose cryptococcosis and also to decide what clinical information to share with the laboratory according to each situation. We will provide the national health system with a resource for the diagnosis of cryptococcosis, instead of empirical treatment when routine treatment is not available. Therefore, the clinician is free to request routine or experimental testing. If the clinician decides to request a urine sample for the diagnosis of cryptococcosis, the laboratory will provide feedback according to the clinician's request in order to follow up on the patient.

The implementation of the diagnosis of cryptococcosis with Chinese ink using non-invasive urine samples at the selected sites will take place over 6 months. In this implementation phase, the health professionals assigned to the medical service with knowledge of the intervention (new test for cryptococcosis) will request that it be carried out by colleagues from the laboratory who have been previously trained in its execution. Throughout this phase (Figure 2) monitoring of clinicians' behaviour in relation to the use of the new diagnostic will take place and documentation of its implementation will be captured (Appendix V).

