# Evaluation of the RE-AIM-based implementation of the technique of laboratory diagnosis of cryptococcosis using the China ink method in urine as a point of care in southern Mozambique

This is a cross-sectional quantitative study aimed at measuring the contribution of the diagnosis introduced (intervention effect) in the six hospitals (MCH, MGH, JMGH, MPH, XPH and CHC) over three months. Sampling will be non-probabilistic, intentional with regard to the participants (healthcare professionals) and by convenience concerning the study sites.

In the Implementation Evaluation Phase (Post-implementation), during three months the implementation will be evaluated using the RE-AIM conceptual framework with five domains reach (comprehensiveness), effectiveness, adoption (acceptability and representativeness), implementation and maintenance (sustainability) of the intervention in the hospitals. Data collection will be based on previously prepared questionnaires and standardized scripts coupled to the REDCap platform loaded onto the tablet.

- Reach will be calculated through the proportion of individuals covered by the intervention (clinicians and laboratory technicians).
- Efficacy will be assessed by checking laboratory and clinical results, time to diagnosis and satisfaction of health professionals.

The study includes an evaluation at the beginning (baseline) pre-implementation and at the end post-implementation, where laboratory and clinical results, time to diagnosis and satisfaction of health professionals will be verified at both times. The efficacy of the intervention will therefore be evaluated before and after implementation. WHO recommendations will be consulted, which recommend screening and treatment to prevent complications from a cryptococcal infection. The test to be implemented will contribute to starting treatment on the same day as the consultation and based on the aetiological diagnosis.

- Adoption will be explored through the representativeness of the services that have adopted the implementation including sample flow, laboratory processing and feedback, use of scripts drawn up and made available during the intervention.
- A Likert scale will also be used to analyze the satisfaction of all health professionals covered by the intervention during the study period (clinicians and laboratory technicians).

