**QUESTIONÁRIO**

**Código ___ ___ ___/_______/_____/202___**

**AVALIAÇÃO DA INTERVENÇÃO**

**(Técnico de Laboratório)**

1. **Avalie o seu nível de confiança ao efectuar o exame de tinta de China usando urina**

****Muito confiante Confiante Neutro Inseguro Muito inseguro

1. **As ferramentas disponibilizadas no treino são mais esclarecedores no âmbito de diagnóstico e tratamento da criptococose**

Concordo fortemente Concordo Neutro Descordo Descordo fortemente

1. **A intervenção é uma alternativa recomendável para triagem laboratorial da Criptococose**

Concordo fortemente Concordo Neutro Descordo Descordo fortemente

1. **Desde a sua implementação o teste da tinta-da-China a partir da urina esteve sempre disponível no Hospital**

Concordo fortemente Concordo Neutro Descordo Descordo fortemente

1. **Qualidade dos serviços melhorou com o novo diagnóstico laboratorial**

Concordo fortemente Concordo Neutro Descordo Descordo fortemente

1. **Pode-se estimar a percentagem de pacientes beneficiados pela intervenção em:**

 100%  80 – 99% 50 – 79%  <50%

1. **Avalie a sua satisfação em relação ao diagnostico laboratorial com a técnica da tinta da China usando a urina**

Muito satisfeito Satisfeito Neutro insatisfeito Muito insatisfeito

1. **Avalie a sua satisfação em relação a clareza e legibilidade dos exames solicitados pelo clínico?**

Muito satisfeito Satisfeito Neutro insatisfeito Muito insatisfeito

1. **Avalie a sua satisfação em relação a disponibilidade dos clínicos quando você tenta contatá-los?**

Muito satisfeito Satisfeito Neutro insatisfeito Muito insatisfeito

1. **Avalie a sua satisfação em relação ao tempo de resposta do laboratório**

Muito satisfeito Satisfeito Neutro insatisfeito Muito insatisfeito

1. **Avalie a sua satisfação em relação ao formulário de solicitação dos enxames laboratoriais**

Muito satisfeito Satisfeito Neutro insatisfeito Muito insatisfeito

1. **A qualidade do diagnóstico foi consistente em todos os turnos? (horário de trabalho, fim de semana, feriado, plantão noturno)**

Concordo fortemente Concordo Neutro Descordo Descordo fortemente

1. **Na sua opinião em qual turno, a qualidade do serviço do laboratório foi comprometida?**

Horário de trabalho Fim de semana Feriado Plantão noturno NA

1. **Com a introdução da nova abordagem do diagnóstico o número de óbitos reduziu**

Concordo fortemente Concordo Neutro Descordo Descordo fortemente

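### Annex V asks all covered staff to rate the urine India ink test without recording whether they ever used it, so the pooled satisfaction frequency cannot be read as users' satisfaction

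*Protocol*

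**What the plan says.** In the Protocol's section 7.9, third sub-study (RE-AIM evaluation), satisfaction is part of efficacy: "Efficacy will be assessed by checking laboratory and clinical results, time to diagnosis and satisfaction of health professionals". The same sub-study says who is asked: "A Likert scale will also be used to analyze the satisfaction of all health professionals covered by the intervention during the study period". The analysis given under Quantitative data analysis is descriptive: "And the frequencies of the information obtained will be calculated". No split by use of the test is stated.

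Use is voluntary. The second sub-study leaves the choice of patients to the clinician and adds: "Therefore, the clinician is free to request routine or experimental testing".

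Annex V holds the instrument, in two forms.

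- **Clinician form.** It asks "Avalie a sua satisfação em relação ao diagnostico laboratorial com a técnica da tinta da China usando a urina", with the answers "Muito satisfeito Satisfeito Neutro insatisfeito Muito insatisfeito".
- **Laboratory technician form.** It opens with "Avalie o seu nível de confiança ao efectuar o exame de tinta de China usando urina" and later repeats the satisfaction item on the urine test.

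Neither form has a question on the respondent's own use, and none of these items has a not-applicable option. Both forms do offer NA on the item asking in which shift quality was compromised.

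**The concern.** A clinician who was trained but never requested the urine test still receives a form asking how satisfied he or she is with it. If that person answers, the answer is counted with those of colleagues who used the test. The form gives no way to separate the two groups afterwards.

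The resulting frequency enters the efficacy domain of RE-AIM. A reader will take it as the experience of people who worked with the test. A low value could mean that users disliked the test, or that few people used it and the rest chose the midpoint. A high value could come from non-users giving an agreeable answer, a tendency the Protocol itself recognises under Study limitation.

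Two features of the design add to this.

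- **Unequal opportunity to use the test.** In Table 1, follow-up after the implementation month is 8 months at MCH and 3 months at CHC. If the forms are completed in the common final evaluation, staff at late hospitals have had less time to use the test.
- **Small numbers.** The Sample and Sampling section lists between 2 and 8 clinicians per hospital, so one non-user weighs heavily.

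**Working it through.** The Protocol gives no figure for uptake or satisfaction, so there is no stated result to reproduce. The check has two parts.

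**1. Can the study's documents separate users from non-users?**

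- *Annex V, both forms:* no item on own use. The second sub-study says that monitoring of clinicians' use will be documented in Appendix V, but the Annex V forms do not ask for it.
- *Annex IV:* asks how often the clinician requests the test, but it belongs to the situation assessment before implementation.
- *Variables and data analysis plan:* tests requested and adherence are recorded, and adherence is modelled against characteristics of the professional. No link to the satisfaction answers is stated.
- *Linkage:* the Annex V forms carry a code field, and the Confidentiality section assigns unique IDs. The Study limitation section calls the questionnaires anonymous. Linkage is possible but not planned in the text.

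**2. How far could the pooled figure move?**

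Let *u* be the share of respondents who used the test, *s* the share of users who are satisfied, and *q* the share of non-users who tick satisfied. If everyone answers:

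reported satisfaction = *u·s* + (1 − *u*)·*q*

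All three inputs are assumptions. With *s* = 80%:

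| Use *u* | All non-users neutral (*q* = 0) | Half satisfied (*q* = 50%) | All satisfied (*q* = 100%) | Blank, or as users |
|---|---|---|---|---|
| 90% | 0.9 × 0.8 = 72% | 72% + 5% = 77% | 72% + 10% = 82% | 80% |
| 70% | 0.7 × 0.8 = 56% | 56% + 15% = 71% | 56% + 30% = 86% | 80% |
| 50% | 0.5 × 0.8 = 40% | 40% + 25% = 65% | 40% + 50% = 90% | 80% |

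The reverse calculation shows why the figure cannot be interpreted. With *q* = 0, a reported 40% fits *s* = 0.40/0.50 = 80% at half use, *s* = 0.40/0.75 = 53% at three-quarters use, and *s* = 40% at full use.

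On the base, the staff list under Sample and Sampling gives 8 + 4 + 4 + 3 + 3 + 2 = 24 clinicians and 6 × 2 = 12 technicians, 36 in all. One non-user is 1/8 = 12.5% of clinician answers at MCH and 1/2 = 50% at CHC.

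**The case against.** The strongest reply is that asking everyone is deliberate. The Protocol's Likert item follows the Adoption bullet, and a trained clinician who declines the test because of distrust is informative about acceptability. Restricting to users also brings its own bias: dissatisfied clinicians may stop requesting, so satisfaction among users can look high because others rejected the test. This stands, and it rules out a users-only figure as the sole efficacy measure.

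Several narrower replies also stand.

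- The items on response time, staff availability, the request form and report clarity concern general laboratory service. The closing item concerns the intervention as a whole, which includes training, guides and information flow. Non-users can answer all of these.
- The freedom to choose belongs to clinicians. Technicians perform the test on request, and nothing in the text shows that any would have performed none. Confidence could also be rated after training alone.
- Nothing makes the items compulsory, so it cannot be said that non-users have to rate the test.
- No comparison of satisfaction between hospitals is specified.

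A further reply is that use is recorded elsewhere and that a split by use could be left to the statistical analysis plan. The split could. Whether the answers can be linked to use is a matter of data collection, and a plan written later may be unable to recover it if the forms are handled as anonymous.

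A reader might infer that the satisfaction result merely tracks uptake and says nothing about satisfaction. The documents do not support that. The result depends on uptake, on users' satisfaction and on non-users' answers, and it follows uptake closely only if non-users mostly choose the neutral or a negative answer.

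**Conclusion.** The point holds for the test-specific items: satisfaction with the urine test on both forms and, with less force, technicians' confidence in performing it. The pooled frequency can mix users with non-users and cannot be read as users' satisfaction. The general laboratory-service items and the overall intervention item are not affected in the same way.

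The direction and size of the distortion are unknown. The 40% to 90% span at half use rests on an assumed 80% satisfaction among users and on two opposite, all-or-nothing patterns of answering by non-users. It shows what the instrument would allow and is not a forecast. With full uptake, or with non-users who skip the item or answer as users do, there is no distortion.

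Satisfaction is one of several efficacy components, so this does not undermine the evaluation as a whole. It should still be corrected before the forms are used, because the flaw lies in the instrument and may not be repairable afterwards.

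**What to change.** 1. On both Annex V forms, add one item on the number of urine India ink tests the respondent has requested (clinician) or performed (technician), with none as an answer.
2. Add a not-used / not-applicable option to the test-specific satisfaction and confidence items only. Keep putting all other items to all covered staff.
3. Report satisfaction with the test among users, and overall satisfaction with the intervention for all staff split by use, with the number of non-users beside both.
4. State that the users-only figure is itself selected and is not the sole efficacy measure from this questionnaire.

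The cost is one extra item and an added answer option in REDCap. The test-specific percentage will rest on fewer respondents, from a base of only 24 listed clinicians and 12 technicians, so counts should be shown with the percentages.

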**Obrigado pela colaboração.**

**Anexo V**  **Versão 04, Outubro 2023**

**Implementação da técnica de tinta da China em urina para triagem laboratorial *point-of-care* da Criptococose em pacientes adultos infectados por HIV no sul de Moçambique.**

**QUESTIONÁRIO**

**Código ___ ___ ___/_______/_____/202___**

**AVALIAÇÃO DA INTERVENÇÃO**

**(Técnico de Laboratório)**

1. **Avalie o seu nível de confiança ao efectuar o exame de tinta de China usando urina**

****Muito confiante Confiante Neutro Inseguro Muito inseguro

1. **As ferramentas disponibilizadas no treino são mais esclarecedores no âmbito de diagnóstico e tratamento da criptococose**

Concordo fortemente Concordo Neutro Descordo Descordo fortemente

1. **A intervenção é uma alternativa recomendável para triagem laboratorial da Criptococose**

Concordo fortemente Concordo Neutro Descordo Descordo fortemente

1. **Desde a sua implementação o teste da tinta-da-China a partir da urina esteve sempre disponível no Hospital**

Concordo fortemente Concordo Neutro Descordo Descordo fortemente

1. **Qualidade dos serviços melhorou com o novo diagnóstico laboratorial**

Concordo fortemente Concordo Neutro Descordo Descordo fortemente

1. **Pode-se estimar a percentagem de pacientes beneficiados pela intervenção em:**

 100%  80 – 99% 50 – 79%  <50%

1. **Avalie a sua satisfação em relação ao diagnostico laboratorial com a técnica da tinta da China usando a urina**

Muito satisfeito Satisfeito Neutro insatisfeito Muito insatisfeito

1. **Avalie a sua satisfação em relação a clareza e legibilidade dos exames solicitados pelo clínico?**

Muito satisfeito Satisfeito Neutro insatisfeito Muito insatisfeito

1. **Avalie a sua satisfação em relação a disponibilidade dos clínicos quando você tenta contatá-los?**

Muito satisfeito Satisfeito Neutro insatisfeito Muito insatisfeito

1. **Avalie a sua satisfação em relação ao tempo de resposta do laboratório**

Muito satisfeito Satisfeito Neutro insatisfeito Muito insatisfeito

1. **Avalie a sua satisfação em relação ao formulário de solicitação dos enxames laboratoriais**

Muito satisfeito Satisfeito Neutro insatisfeito Muito insatisfeito

1. **A qualidade do diagnóstico foi consistente em todos os turnos? (horário de trabalho, fim de semana, feriado, plantão noturno)**

Concordo fortemente Concordo Neutro Descordo Descordo fortemente

1. **Na sua opinião em qual turno, a qualidade do serviço do laboratório foi comprometida?**

Horário de trabalho Fim de semana Feriado Plantão noturno NA

1. **Com a introdução da nova abordagem do diagnóstico o número de óbitos reduziu**

Concordo fortemente Concordo Neutro Descordo Descordo fortemente

1. **A nova abordagem do diagnóstico contribuiu para que maior número de indivíduos vivendo com HIV tivessem oportunidade de testar para *Criptococcus***

Concordo fortemente Concordo Neutro Descordo Descordo fortemente

1. **Avalie na generalidade a sua satisfação em relação a intervenção no seu hospital**

Muito satisfeito Satisfeito Neutro insatisfeito Muito insatisfeito

**Obrigado pela colaboração.**
